### Participant timeline {13}

The flowchart in Fig. 1 describes the participant timeline throughout the study.

**Fig. 1 Fig1:**
[figure not shown]
Flow diagram describing the participant timeline through CATHETER II

### Sample size {14}

We have used information from a survey of experts and patients and also from available literature to decide that for washouts to be worthwhile there must be a reduction in LTC blockage of 25% [1] (and personal communication, Cambridge PPI group survey). In our case, this would be a reduction in the rate of blockage from 11.8 per 1000 days (unpublished data, [name], [name], 2018) to 8.9 per 1000 days. Participants will be followed up for 2 years. The trial has a 90% power and a significance level of 2.5%. The number of blockages has a negative binomial distribution with a dispersion parameter of 0.6. Recruiting 200 participants per arm allows for approximately 50 out of 730 loss to follow-up days. All available days of follow-up are to be used. The formula from Zhu and Lakkis [21] was used to calculate the sample size for comparing two negative binomial rates.

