### Objectives {7}

The aim of the study is to determine whether the addition of a policy of prophylactic weekly catheter washouts to current standard LTC care improves the outcome of care for people living with a LTC in the UK.

The hypotheses being tested are:Does a policy of weekly prophylactic normal saline catheter washouts plus standard LTC care result in a relative reduction of 25% (or more) in catheter blockage requiring intervention compared to standard LTC care alone?Does a policy of weekly prophylactic acidic catheter washouts plus standard LTC care result in a relative reduction of 25% (or more) in catheter blockage requiring intervention compared to standard LTC care alone?

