### Trial design {8}

CATHETER II is a pragmatic three-arm, parallel-group, open multi-centre superiority randomised controlled trial. It compares the clinical and cost-effectiveness, patient acceptability and satisfaction, and safety of weekly prophylactic catheter washouts policies in addition to standard long-term catheter (LTC) care compared to standard LTC care only, in adults living with LTC.

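### The 2.5% significance level has no stated sidedness: 200 per arm gives 90% power if it is one-sided, but only about 85% if it is two-sided for each of the two primary comparisons

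*Protocol article*

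**What the plan says.** The Sample size section {14} of the protocol article gives the level and the power in one sentence: "The trial has a 90% power and a significance level of 2.5" per cent. The effect is "a reduction in the rate of blockage from 11.8 per 1000 days" "to 8.9 per 1000 days". The count is taken as negative binomial with dispersion 0.6, follow-up is two years, and the method is the Zhu and Lakkis formula for two negative binomial rates. On size it says "Recruiting 200 participants per arm allows for approximately 50 out of 730 loss to follow-up days".

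The Objectives section {7} opens with "The hypotheses being tested are" and lists two questions: saline washout against standard care, and acidic washout against standard care. Each asks about a relative reduction of 25% or more. The Trial design section {8} describes a "pragmatic three-arm, parallel-group, open multi-centre superiority randomised controlled trial". Allocation is 1:1:1, so each comparison has equal arms and both share the control arm.

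No section gives the sidedness of the 2.5%, calls it a share of 5%, or states a multiplicity rule or confidence level for the primary outcome. The Statistical methods section {20a} names the primary model without a threshold.

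**The concern.** A significance level given without qualification is ordinarily read as two-sided. Here there are exactly two primary comparisons, and 2.5% is exactly half of 5%. The natural reading is therefore a two-sided 5% level divided between the two comparisons. On that reading the printed 90% power does not follow from the printed inputs.

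Two things depend on the missing word. One is the power: a type II error of 10% or of about 15%. The other is the success criterion: a two-sided primary p-value between 0.025 and 0.05 is positive on one reading and negative on the other. In an open trial that choice should be fixed before results are seen.

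**Working it through.** **Inputs (Sample size {14}).** Control rate r0 = 0.0118 per day; washout rate r1 = 0.0089 per day; dispersion k = 0.6, used as variance = μ + kμ²; mean exposure t = 730 − 50 = 680 days; equal arms.

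**Formula (Zhu and Lakkis).**

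n per arm = (z_α √V0 + z_β √V1)² / [ln(r1/r0)]², with V1 = (1/t)(1/r0 + 1/r1) + 2k.

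V0 is the variance under the null. The method offers three choices: reference-group rate, true rates, or maximum likelihood. With true rates, V0 = V1.

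**Common quantities.**
- V1 = (84.746 + 112.360)/680 + 1.2 = 0.28986 + 1.2 = 1.48986
- ln(8.9/11.8) = −0.28205; squared, 0.07955
- z_β for 90% power = 1.2816

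**Step 1: reproduce the plan's figure (z_α = 1.960: one-sided 2.5%, or two-sided 5%).** With true rates:
- n = (1.960 + 1.2816)² × 1.48986 / 0.07955 = 196.8
- standard error of the log rate ratio at 200 per arm = √(1.48986/200) = 0.08631
- power at 200 = Φ(0.28205/0.08631 − 1.960) = Φ(1.308) = 90.5%

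The stated 200 and 90% are reproduced.

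**Step 2: two-sided 2.5% (z_α = 2.2414).** With true rates:
- n = (2.2414 + 1.2816)² × 1.48986 / 0.07955 = 232.4
- power at 200 = Φ(3.268 − 2.241) = Φ(1.027) = 84.8%

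**Step 3: all three null-variance choices (680 days, 8.9 per 1000).**

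| Null variance | n, z = 1.960 | Power at 200 | n, z = 2.241 | Power at 200 |
|---|---|---|---|---|
| Reference-group rate | 193.5 | 90.9% | 228.4 | 85.5% |
| True rates | 196.8 | 90.5% | 232.4 | 84.8% |
| Maximum likelihood | 196.3 | 90.5% | 231.9 | 84.9% |

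**Step 4: can 200 be rescued at two-sided 2.5%?**
- Full 730 days, 8.9 per 1000: n = 226 to 229, power 85.3% to 85.9%.
- 680 days, exact 25% reduction (8.85 per 1000): n = 220 to 224, power 86.2% to 86.9%.
- 730 days, exact 25% reduction and the most favourable variance: n = 217, power 87.4%.
- Reading 0.6 as a reciprocal (k = 1/0.6) needs 561 to 565 per arm at 680 days, and k = √0.6 needs 283 to 287. k = 0.36 needs only 154 to 158, so none of these gives 200.
- To reach 200 per arm with 90% power at 680 days and 8.9 per 1000, k would have to be about 0.50 to 0.51.

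**Step 5: family-wise error.** With equal arms and a shared control, the two test statistics have correlation 0.5 under the joint null. From the bivariate normal:

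| Critical value per comparison | Any false claim of benefit | Any false rejection, either direction |
|---|---|---|
| 1.960 | 4.5% | 9.1% |
| 2.241 | 2.3% | 4.6% |

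**The case against.** The strongest reply is that nothing printed is wrong. Read 2.5% as one-sided and every figure in the section agrees: about 194 to 197 per arm, rounded up to 200, with at least 90% power. The hypotheses are directional and the trial is called a superiority trial, so this reading is open. Its family-wise error for a false claim of benefit is 4.5%, which can be seen as one-sided 5% split in two. All of this stands. A reader might infer that the sample size was miscalculated, or that no reading fits all the printed claims. The document supports neither.

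A reader might also infer that the trial promises a two-sided 5% family-wise error and breaks it. It makes no such promise: there is no mention of Bonferroni, of 97.5% intervals or of an overall 5% level. Whether two different washouts against a shared control need adjustment is itself debated. The 9.1% is therefore a consequence to disclose on the one-sided reading, not an error.

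Finally, sidedness and multiplicity are often set in the analysis plan or the full protocol, which are not shown, and they may be set there. That limits the point to what this article prints. But the article gives level, power and N together as its justification, and those three figures agree on one reading and not on the more usual one.

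**Conclusion.** The point holds as an ambiguity with a measurable consequence. On the one-sided reading the stated power is correct (90.5% to 90.9% at 680 days). On the two-sided reading, which is the more natural one with two comparisons, it is about 85%, and at most 87.4% under the most favourable exposure and rounding. The type II error is then about 15% where 10% is stated, roughly half as large again.

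These figures take the planning rates and k = 0.6 at face value and give every participant the mean exposure of 680 days. The family-wise figures assume correlation 0.5 and large-sample normality. The calculation cannot show which level was intended; it shows only that 200 per arm matches z = 1.96.

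**What to change.** State in the Sample size section whether 2.5% is one-sided or two-sided, and whether it is 5% divided over the two primary comparisons. Then:

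- **If two-sided 2.5% per comparison:** restate the power as about 85% per comparison at 200 per arm, and report 97.5% confidence intervals for both primary comparisons.
- **If one-sided 2.5% per comparison:** keep 90%, but say that this equals two-sided 5% per comparison and gives a family-wise error of about 4.5% for a false claim of benefit (9.1% two-sided).

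Carry the same threshold into the analysis section and the analysis plan before data lock. The cost is wording only. Neither branch requires a change in N or in trial conduct; on the two-sided branch the price is a lower stated power.

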LTC can be associated with several adverse events [5] which affect the daily life of patients and can consume substantial NHS resources [8]. Wilde et al. reported typical adverse events of LTC blockage (34% of participants): symptomatic catheter-associated urinary tract infections (S-CAUTI), whether or not this has been proven bacteriologically (57%); accidental dislodgment (28%); urinary leakage (67%); bladder spasms (59%); kinks/twists (42%) and pain (49%) [1].

LTC blockages often occur secondary to the formation of encrustations on the luminal and outer surfaces of the catheter, with an incidence of 40–50% in patients in most studies [7, 9–11]. Wilde et al. in 2017 [1] assessed 202 patients with LTC over 12 months and showed that 34% of patients reported blockage and a rate of 8.54/1000 days of catheter use. Catheter blockage is considered a medical emergency and can lead to distress, autonomic dysreflexia in patients with spinal cord injury at or above T6, increased healthcare utilisation and urosepsis [12]. Current best practice for the management of LTC blockage requires a regular (and more frequent) change of the catheter [3]. Catheter washouts are often used in these cases despite the lack of evidence on their benefit, potential harm, best solution to be used, appropriate volume and frequency, and individual impact on quality of life among patients with LTC [2].

Several catheter washouts policies are used in clinical practice for the prevention and/or management of LTC blockage. Washouts used are of different types (normal saline, acidic, antimicrobial), volumes and frequency of administration. The Cochrane review [2] assessed the best available evidence and concluded that there is insufficient evidence to determine whether prophylactic catheter washout policies had a beneficial or harmful effect on any of the outcomes in patients with LTC. The authors recommended a rigorous and methodologically robust randomised controlled trial to assess the clinical and cost-effectiveness of washout policies in patients with LTC.

Muncie et al. [13] compared saline washouts versus no washouts policy over 24 weeks in a limited population and showed no significant differences in S-CAUTI per 100 days of catheter use. Concerns exist that the use of washouts can damage the bladder mucosa and possibly increase the risk of S-CAUTI. NICE CG139 recommend that “[catheter] washouts must not be used to prevent catheter-associated infections” [3].

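### The 90% power rests on a dispersion of 0.6 that does not fit the protocol's own 12-month blockage figures, so it holds only conditionally on that input

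*Protocol article*

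**What the plan says.** The Sample size section (item 14) plans for "a reduction in the rate of blockage from 11.8 per 1000 days" "to 8.9 per 1000 days". It then states "The trial has a 90% power and a significance level of 2.5"%, without saying whether the level is one- or two-sided. On follow-up it says "Participants will be followed up for 2 years" and "Recruiting 200 participants per arm allows for approximately 50 out of 730 loss to follow-up days", so about 680 days per person are used. The variance assumption is "The number of blockages has a negative binomial distribution with a dispersion parameter of 0.6". The article ties the control rate of 11.8 to unpublished data; it does not say where 0.6 comes from.

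The Background section (item 6a) describes a cohort of 202 catheter users followed "over 12 months and showed that 34% of patients reported blockage and a rate of 8.54/1000 days" of catheter use. It also describes blockage from encrustation "with an incidence of 40–50% in patients in most studies", with no time window.

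The primary analysis (item 20a) is a negative binomial regression adjusted for the minimisation covariates. One of these is previous blockage in the last 6 months, coded none versus one or more (item 16a).

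**The concern.** In a negative binomial model, the mean and the dispersion together fix the share of people with no event. A high mean rate combined with a majority who never block means that events are concentrated in a minority, and that requires a large dispersion. The Background describes that pattern, while the Sample size section assumes a much more even spread. Dispersion supplies about four fifths of the variance in the planning formula, so the power is very sensitive to it.

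Both hypotheses in the Objectives (item 7) turn on a 25% reduction. If the dispersion is well above 0.6, a trial of this size could miss such a reduction more often than the stated 90% suggests, and a non-significant result would say less about the 25% target than a reader would assume.

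**Working it through.** **Inputs.** From the Sample size section: r1 = 0.0118 and r2 = 0.0089 per day, t = 680 days, k = 0.6, n = 200 per arm, level 2.5%, power 90%. From the Background: 34% with any blockage and 8.54 per 1000 days, in a cohort assessed over 12 months; and 40–50% in other studies, window not given.

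**1. Reproducing the plan's figure.** The cited approach for two negative binomial rates is, in its true-rates form:

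V = 1/(r1·t) + 1/(r2·t) + 2k, and n = (z_α + z_β)²·V / ln(r2/r1)².

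- V = 0.125 + 0.165 + 1.20 = 1.49, of which 1.20 is the dispersion term.
- ln(8.9/11.8) = −0.282, squared 0.0796.
- One-sided 2.5%: (1.960 + 1.282)² × 1.49 / 0.0796 = 197 per arm. Power at 200 is 90.5%.
- Two-sided 2.5%: (2.241 + 1.282)² × 1.49 / 0.0796 = 232 per arm. Power at 200 is about 85%.
- Reading 0.6 as the inverse (k = 1.67) would need 479 per arm one-sided, so 0.6 was used as the multiplier in variance = μ + kμ².

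The arithmetic is sound on the one-sided reading.

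**2. What k = 0.6 predicts.** P(at least one blockage) = 1 − (1 + kμ)^(−1/k).

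- At 8.54/1000 over 365 days, μ = 3.12, and 1 − (1 + 0.6 × 3.12)^(−1/0.6) = 83%.
- At 11.8/1000 over 365 days, μ = 4.31, giving 88%.
- The cohort reports 34%.

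**3. The k that matches.** Solving (1 + kμ)^(−1/k) = 1 − share blocking, with a 12-month window throughout. For the 40–50% figures this window is an assumption.

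| Share blocking | k at 8.54/1000, all patients | k at 11.8/1000, all patients | k if 8.54 is the rate among blockers only |
|---|---|---|---|
| 34% | 7.8 | 8.8 | 4.0 |
| 40% | 5.8 | 6.6 | 3.1 |
| 50% | 3.6 | 4.3 | 2.1 |

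The 40–50% rows therefore span about 2 to 7. The middle column pairs shares and a rate from different sources and is illustrative only.

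**4. Power at 200 per arm.** Power = Φ(√200 × 0.282/√V − z_α), same rates and follow-up.

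| k | V | One-sided 2.5% | Two-sided 2.5% |
|---|---|---|---|
| 0.6 | 1.49 | 90.5% | 85% |
| 1 | 2.29 | 75% | 65% |
| 2 | 4.29 | 49% | 38% |
| 4 | 8.29 | 28% | 20% |
| 7.8 | 15.89 | 17% | 11% |

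At k = 2, the rate ratio detectable with 90% power (one-sided) is about 0.62: V = 0.125 + 1/(0.0118 × 0.62 × 680) + 4 = 4.33, and exp(−3.242 × √(4.33/200)) = 0.62. That is a 38% reduction.

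**5. Allowing for covariate adjustment.** The figures in step 4 use the marginal dispersion, but the planned model adjusts for previous blockage. A simulation gave each participant a stable gamma-distributed personal rate, a 6-month history coded 0 versus ≥1, and 680 days of follow-up (300 trials per k). One-sided 2.5% power was about 66%, 50% and 35% at k = 2.1, 4 and 7.8. The Monte Carlo standard error is at most √(0.25/300) = 2.9 points. Median residual dispersion was 1.0, 1.5 and 2.0. Holding each person's rate constant favours the adjustment.

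As an extreme case, suppose only 34–50% of participants ever block, k is 0.6 among them, and history identifies them perfectly. With a share p blocking, V = p/(r1·t) + p/(r2·t) + 1.2 and the effective n is 200p. One-sided power is then 53% at p = 0.34 and 68% at p = 0.50.

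**The case against.** Several counter-arguments have force.

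- **The window.** The phrase about 12 months describes how long the cohort was assessed, and the same 34% appears earlier in the Background with no window. If it covered about 55 days, k = 0.6 would fit. At 60 days, k = 0.6 predicts 36%, within one standard error of 34% (√(0.34 × 0.66/202) = 3.3 points). This stands as a possibility, but the article's wording points to 12 months and nothing in it gives a shorter window.
- **The population.** The rate of 11.8 comes from unpublished data, and 0.6 may too. The trial excludes some spinal cord injuries and counts only blockages that needed intervention. External figures can put 0.6 in question, but they cannot fix this trial's dispersion. This stands.
- **Indirect inference.** Deriving k from one zero-proportion assumes the negative binomial shape. With a group of never-blockers, that k need not describe those who do block. The relevant dispersion is also the residual one, after adjustment for more covariates than the one simulated. This limits any exact power figure, but neither check in step 5 comes near 90%.
- **A condensed article.** That the source of 0.6 is not given is no fault in itself, since the full protocol may give it. The point here is a conflict between two stated figures.

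A reader might infer more than the document supports: that the sample size is miscalculated, that 0.6 is impossible, that the 40–50% figure is independent confirmation, or that the true power is 10–17%. The calculation reproduces. The 40–50% has no window. The lowest power figures take the largest marginal k without adjustment, and the 10–11% values also need the two-sided level, which does not reproduce 200 per arm. Nor does the article say that a null result will be read as ruling out a 25% effect.

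**Conclusion.** The point holds in a limited form. The 90% power is correctly computed from its inputs at one-sided 2.5%, but the dispersion of 0.6 conflicts with the cohort described in the Background: 83% predicted to block in 12 months against 34% reported. Read as written, that cohort implies a marginal k of about 4 to 7.8, for which adjusted one-sided power is roughly 35–50%. The lowest value from a 12-month reading, about 2.1, gives roughly 66%.

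These sizes depend on the negative binomial form, on a 12-month window, and on the trial population resembling the cited one. The exact power is therefore unknown. What can be said is that 90% is conditional on an input the article's own figures call into question, and that the favourable 12-month readings examined do not restore it.

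**What to change.** 1. In the Sample size section, reconcile 0.6 with the 34% and 8.54 per 1000 days in the Background (by source, population, definition or time window), or restate the 90% power as conditional on k = 0.6.
2. State whether the 2.5% is one- or two-sided.
3. Give power and the detectable rate ratio at 200 per arm over a range of k, for example 0.6 to 8, for both the marginal and the covariate-adjusted dispersion.
4. Estimate the pooled dispersion, blind to arm, from the internal pilot and the monthly data, and use it to restate the detectable effect before the analysis. This needs no unblinding and no adjustment of the significance level.
5. State that a non-significant result will be judged against the 25% target from its confidence interval.

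The cost is wording and one blinded calculation. No extra participants are needed. The downside is that the stated power is likely to look less favourable.

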### Recruitment {15}

We are recruiting participants from GP practices, secondary and tertiary care hospitals, community hospitals and care homes including nursing homes. Recruitment strategies differ between sites depending on local geographic and NHS organisation factors. Potential participants may be identified by database searches; A&E or in urology, neurorehabilitation and care of the elderly outpatient clinics and wards; and from continence clinics and district nurse and community nurse teams. Potential participants are approached and provided with an invitation letter and a short patient information leaflet. A follow-up telephone call or reminder letter may be sent. In care homes, the care home manager identifies potentially eligible individuals who are approached and provided with a patient information leaflet. Across all settings, a study poster may be displayed as a resource to support recruitment.

Participants may also be recruited through research registries and advertising campaigns utilising methods such as social media, mainstream media, websites and newsletters and with the support of digital marketing agencies. Potential participants identified in this way are referred to a suitable local recruiting site, if one is available, or recruited centrally with all study activities delivered remotely and with clinical oversight by the chief investigator.

All participants are provided with a full patient information leaflet. Eligibility is confirmed and consent is taken prior to baseline data collection and randomisation.

If a participant requires help from a relative, friend, or another informal carer to administer the washouts or complete the patient questionnaires or catheter diary, the relative, friend, or another informal carer is also provided with a patient information leaflet and consented to the study.

An internal pilot with stop/go criteria is embedded to establish whether the projected recruitment rate is achievable.

### Assignment of interventions: allocation

#### Sequence generation {16a}

Participants are allocated 1:1:1 to one of the three trial arms by a member of the local research team using a centralised computerised randomisation system (administered by the Centre for Healthcare Randomised Trials (CHaRT), University of Aberdeen. Random allocation uses the minimisation covariates: region; gender; age (< 45 years, 45–64 years and ≥ 65 years); residential status (care home vs community); previous blockages requiring intervention in the last 6 months (0 vs ≥ 1); previous S-CAUTI requiring antibiotics in last 6 months (0 vs ≥ 1); Urine pH (normal vs acidic vs alkaline vs not available).

#### Concealment mechanism {16b}

The allocation sequence is concealed by the use of a centralised computerised randomisation system.

#### Implementation {16c}

Delegated site personnel will enrol participants on the study website in which the randomisation system is embedded. The centralised computerised randomisation system generates the allocation sequence and assigns the trial arm.

